### Study aims and hypotheses

1.1

The primary objective of this RCT is to evaluate the immediate efficacy of the SAF-T intervention in alleviating psychological distress (a composite of stress, anxiety, and depressive symptoms) among family members of ICU patients, as measured on Day 3 post-enrollment (immediately after intervention completion). Secondary objectives include: (1) To assess the longitudinal trajectories of stress, anxiety, and depressive symptoms in family members receiving the SAF-T intervention, examining its sustained effects at Day 3 post-enrollment (post-intervention), upon patient transfer from the ICU, and at the Day 30 and Day 90 follow-ups. (2) To explore the potential of the SAF-T intervention for preventing PTSD symptoms, measured at Day 3 post-enrollment (post-intervention), upon patient transfer from the ICU, and at the Day 30 and Day 90 follow-ups. (3) To explore the effect of the SAF-T intervention on sleep quality, measured at Day 3 post-enrollment (post-intervention), upon patient transfer from the ICU, and at the Day 30 and Day 30 follow-ups.

Based on the objectives above, the following hypotheses are proposed: (1) Primary Hypothesis: Compared to family members receiving usual care (control group), those receiving the SAF-T intervention will demonstrate a significantly lower composite score of psychological distress after completing the 3-day intervention period (Day 3 post-enrollment). (2) Secondary Hypotheses: (1) Compared to the control group, the intervention group will show greater reductions or faster improvement in individual scores on the perceived stress scale (PSS-10), generalized anxiety disorder scale (GAD-7), and patient health questionnaire (PHQ-9) from baseline to each follow-up assessment. (2) Compared to the control group, the intervention group will have significantly lower impact of event scale-revised (IES-R) scores (indicating fewer PTSD symptoms). (3) Compared to the control group, the intervention group will have significantly lower sleep quality index (PSQI) scores.

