. Finally, the three standardized scores will be summed to obtain the participant’s psychological distress composite score: 
$\text{CompositeScor}e_{i}=Z_{i,\mathrm{PSS}-10}+Z_{i,\mathrm{GAD}-7}+Z_{i,\mathrm{PHQ}-9}.$
 (2) Primary statistical model. The primary between-group comparison at Day 3 will be performed using an analysis of covariance (ANCOVA), with the Day 3 composite score as the dependent variable, experimental group as the fixed factor, and the baseline composite score as a covariate. Prior to ANCOVA, normality of residuals and homogeneity of regression slopes will be assessed. If the assumptions of ANCOVA are violated, a non-parametric alternative (e.g., Quade’s rank ANCOVA) will be applied. (3) Effect size and validation. To assess the clinical significance of the intervention effect, Cohen’s d effect size will be calculated, with *d* = 0.2 considered a small effect, *d* = 0.5 a medium effect, and *d* = 0.8 a large effect (Bartko et al., 1988). As a validation step, the theoretical standard deviation of the composite score will be computed using the variance sum theorem: 
$SD_{\text{theoretical}}=\sqrt{3+2(r_{12}+r_{13}+r_{23})}$
. where 
$r_{12}$
, 
$r_{13}$
, and 
$r_{23}$
 represent the Pearson correlation coefficients between each pair of the three scales. This theoretical value will be compared with the observed standard deviation to confirm the construct validity of the composite score. (4) Sensitivity analyses. As a sensitivity analysis, a per-protocol (PP) analysis will be conducted to evaluate the robustness of the primary ITT results. Additionally, to assess the potential impact of contamination, we will perform an analysis excluding control group participants who received protocol-prohibited psychological support during the intervention window.

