Analysis of Secondary and Longitudinal Outcomes: For longitudinal analyses of secondary outcomes—including the individual trajectories of PSS-10, GAD-7, and PHQ-9 scores, as well as PSQI and IES-R scores across time points (Day 3, discharge, Day 30, Day 90)—linear mixed-effects models (LMMs) will be employed. This approach handles missing data under the missing-at-random (MAR) assumption and accounts for within-subject correlation. Separate LMMs will be fitted for each continuous secondary outcome. Each model will include: (1) Fixed Effects: Treatment group, time (as a categorical factor), the group × time interaction, and the corresponding baseline score of the outcome as a covariate. (2) Random Effects: A random intercept for each participant will be included to account for individual variability. (3) Covariance Structure: An unstructured covariance matrix will be initially specified to model the within-subject errors, with the final structure chosen based on model fit indices (e.g., Akaike Information Criterion). The group × time interaction will be the effect of primary interest, testing whether the change in the outcome over time differs between groups. If the interaction is significant, simple effects analyses (e.g., between-group comparisons at each time point) will be conducted. For the primary ITT analysis, missing outcome data at Day 3 will be handled using the Multiple Imputation (MI) method. Results from analyses on each dataset will be pooled using Rubin’s rules. For longitudinal LMMs, the full-information maximum likelihood (FIML) estimation inherent to the method will be utilized.

Handling of Multiplicity: All analyses of secondary outcomes and longitudinal trajectories are considered exploratory. Results from these analyses will be presented with point estimates and 95% confidence intervals to indicate the magnitude and precision of effects. *p*-values from these exploratory analyses will be interpreted descriptively and with caution, without formal adjustment for multiple testing, to avoid inflating Type II error rates while generating hypotheses for future research.

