Additional Analyses: Intra-group changes from baseline to specific time points for normally distributed data will be assessed using paired *t*-tests, or the *Wilcoxon* signed-rank test for non-normally distributed data. And we will assess the sensitivity of the results to potential contamination by conducting exclusion analysis and reclassification analysis on the control group participants who received additional support.

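### Within-arm tests of change from baseline are planned without condition, while the between-arm comparison at each visit depends on a significant interaction

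*Protocol article*

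**What the plan says.** Four parts of the protocol article bear on this.

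- **Hypothesis (section 1.1).** Secondary hypothesis 1 is comparative: "Compared to the control group, the intervention group will show greater reductions or faster improvement in individual scores" on the PSS-10, GAD-7 and PHQ-9, from baseline to each follow-up.
- **Analysis given to the secondary outcomes (section 2.6).** A linear mixed model is fitted for each scale "across time points (Day 3, discharge, Day 30, Day 90"), with the baseline score as a covariate. "The group × time interaction will be the effect of primary interest, testing whether the change in the outcome over time differs between groups". The visit-level comparison is conditional: "If the interaction is significant, simple effects analyses (e.g., between-group comparisons at each time point) will be conducted".
- **Within-arm tests (section 2.6, Additional Analyses).** "Intra-group changes from baseline to specific time points for normally distributed data will be assessed using paired" t-tests, with the Wilcoxon signed-rank test for non-normal data. No condition, purpose or hypothesis is attached to them.
- **Status (section 2.6, Handling of Multiplicity).** "All analyses of secondary outcomes and longitudinal trajectories are considered exploratory", with estimates and 95% confidence intervals, and with p-values to be read cautiously.

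The primary analysis is separate and between-arm: "The primary between-group comparison at Day 3 will be performed using an analysis of covariance (ANCOVA") adjusted for the baseline composite.

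**The concern.** A paired test within the SAF-T arm asks whether that arm's mean score moved. It uses no control data. Baseline is taken while the relative is in the ICU, and follow-up runs past ICU discharge to Day 90. Scores could therefore fall in both arms without any treatment effect, and the test would then be significant for a reason unrelated to SAF-T.

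This matters mainly because of the imbalance in what gets reported. The uninformative test is always run, and the informative one may not be. The within-arm tests also resemble the hypothesis in wording, since both speak of change from baseline to given visits. A report could therefore show visit-by-visit p-values for change within SAF-T and none for the difference between arms. A randomised comparison that the planned model can supply would be missing from the place where readers look for it.

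**Working it through.** **1. What each analysis tests**

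| Analysis | Null hypothesis | Uses control data? | When run |
|---|---|---|---|
| Paired t / Wilcoxon, per arm | Mean (or typical) change in this arm is zero | No | Always |
| LMM group × time | The between-arm difference is the same at Day 3, discharge, Day 30 and Day 90 | Yes | Always |
| LMM contrast at a visit | Baseline-adjusted difference at that visit is zero | Yes | Only if the interaction is significant |

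The third row answers secondary hypothesis 1. With baseline as a covariate, the adjusted difference in score at a visit equals the adjusted difference in change to that visit.

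**2. How often the visit contrasts would be skipped**

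The model's time levels are the four post-baseline visits. Let the true adjusted benefit be δ at each of them. The interaction compares δ, δ, δ, δ and is exactly zero for any δ. A test at 0.05 is then significant in 5% of trials, so the contrasts for that scale are skipped in 1 − 0.05 = 95%.

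**3. Sample sizes used**

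Section 2.1.2 gives 22 per group, or 28 after loss to follow-up, for d = 1.13, two-sided alpha 0.05 and power 0.95. Normal approximation: 2 × (1.960 + 1.645)² / 1.13² = 20.4, so 21. The exact t calculation gives 22. Then 22 / (1 − 0.20) = 27.5, so 28. The plan's figures are reproduced, and n = 22 and n = 28 are used below.

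**4. Behaviour of the paired test when SAF-T has no effect**

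The documents give no control-arm time course, SD of change or correlation. The inputs here are therefore assumptions: the same decline Δ (in SD units) in both arms, equal SDs, and correlation ρ between baseline and follow-up. The noncentrality of the paired t-test is Δ√n / √(2(1 − ρ)). At ρ = 0.5 the denominator is 1:

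- Δ = 0.3: 0.3 × √22 = 1.41 and 0.3 × √28 = 1.59
- Δ = 0.5: 0.5 × √22 = 2.35 and 0.5 × √28 = 2.65

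The within-arm figures below are exact noncentral t probabilities. The last column comes from 20,000 simulated trials per row and sample size. The SAF-T-only column is p(1 − p), because the two arms are independent with the same p.

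| Decline in both arms | SAF-T paired test significant, n = 22 / 28 | Significant in SAF-T only, n = 22 / 28 | Between-arm ANCOVA significant, n = 22 / 28 |
|---|---|---|---|
| 0 | 5.0% / 5.0% | 4.8% / 4.8% | 5.0% / 4.7% |
| 0.2 SD | 14.6% / 17.5% | 12.5% / 14.4% | 5.1% / 4.9% |
| 0.3 SD | 26.9% / 33.4% | 19.7% / 22.2% | 5.0% / 4.9% |
| 0.5 SD | 60.9% / 72.3% | 23.8% / 20.0% | 5.1% / 4.9% |
| 0.8 SD | 94.7% / 98.3% | 5.0% / 1.7% | 5.0% / 5.1% |

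With ρ varied from 0.3 to 0.7, the within-arm range over both sample sizes is 21% to 51% at 0.3 SD and 47% to 91% at 0.5 SD.

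**The case against.** The other side has a good deal in its favour.

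- **The within-arm tests are not the plan's efficacy tests.** A reader might infer that they are meant to test the secondary hypotheses. The text does not say so. They are listed as additional analyses, tied to no hypothesis, and the ANCOVA and mixed models are the assigned comparisons. This stands.
- **They are not the only visit-level tests in the plan.** The mixed-model contrasts exist, and the model also has a group term. What remains is that they are the only visit-level tests for the secondary scales that are run without a condition.
- **The percentages are not type I error.** It is tempting to read 27% to 72% as a false-positive rate. If both arms truly decline, the paired null is false and rejecting it is correct. The figures are power against an assumed time trend. They show only how often the result would look favourable with no treatment effect.
- **The decline is assumed.** With no decline the rate is 5%. The introduction stresses that PICS-F can persist, so the documents do not establish a spontaneous fall. The SAF-T-only pattern is also not always frequent: at 0.8 SD it falls to 2% to 5%. The protocol nowhere proposes comparing significance between arms.
- **The exploratory label helps in part.** It asks for caution and for estimates with intervals. It does not give a one-arm test information about a between-arm question, and it does not lift the condition on the visit contrasts.
- **The time levels could be read differently.** Section 2.3.2 includes baseline in the longitudinal series. If baseline were a time level in the model, a constant benefit would produce an interaction. Section 2.6, however, lists four post-baseline visits and makes baseline a covariate.

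**Conclusion.** The point holds as a minor one about what gets reported. The within-arm tests cannot bear on secondary hypothesis 1, yet they are unconditional, while the visit comparisons that do bear on it depend on an interaction that a constant benefit would not produce. In that case the visit contrasts for a scale would be skipped in about 95% of trials. This rests on the model as section 2.6 describes it and on an interaction test that holds its 5% level.

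How misleading the remaining p-values could be depends on a time trend that the documents do not give. At an assumed common decline of 0.3 to 0.5 SD with correlation 0.5, the SAF-T paired test is significant in about 27% to 72% of trials with no SAF-T effect, against 5% with no decline.

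A claim that the trial's error rate is inflated would go too far. The Day 3 ANCOVA is untouched, and a between-arm test on the same data stays near 5%.

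**What to change.** Make two changes to section 2.6.

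1. In Additional Analyses, replace the paired t and Wilcoxon tests with a description of within-arm change: mean change with SD or CI, or median and IQR, without p-values. Add a sentence stating that no conclusion on efficacy will be drawn from change within one arm.
2. In the paragraph on secondary and longitudinal outcomes, remove the condition on the visit contrasts. Report the baseline-adjusted between-arm difference with 95% CI at Day 3, ICU discharge, Day 30 and Day 90 from the planned mixed model for each scale, whatever the interaction result. The interaction can still be reported as the test of whether the difference varies over time.

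The cost is a few sentences of wording. No new data, participants or models are needed. The report loses some within-arm p-values.

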### Ethical considerations

2.7

This study received approval from the Medical Ethics Committee, and informed consent was obtained from all research participants. The methods, aim, and potential risks associated with the study were thoroughly explained to the participants. Each participant will sign an informed consent form. Furthermore, all researchers are required to maintain strict confidentiality regarding the participants’ information.

## Discussion

3

Family members of ICU patients frequently serve as primary caregivers and key decision-makers for critically ill individuals, yet they often experience substantial psychological stress manifesting as anxiety or depression. The stress can manifest in symptoms such as anxiety and depression, significantly elevating the risk of developing PICS-F. However, the majority of research conducted on intensive care units predominantly emphasizes patient experiences, often neglecting the significant emotional distress faced by family members. Research indicates that alleviating stress experienced by the families of patients during their stay in the ICU can significantly reduce the incidence of PICS-F (Davidson et al., 2017). The majority of existing intervention studies specifically addressing PICS-F predominantly focus on communication strategies or educational frameworks within the ICU (Rahimi-Bashar et al., 2025). Communication frequently focuses on conveying information to the patient’s family members regarding the current status of the patient’s illness, treatment strategies, and progress. However, it often neglects the provision of psychological and emotional support to the family members. Herein, we present a comprehensive stress management intervention developed by our research team. This study protocol describes a RCT to evaluate the efficacy of the SAF-T intervention in reducing psychological distress among ICU patients’ family members. From a clinical perspective, the brief, manualized SAF-T protocol is designed for potential integration into ICU workflows, offering a scalable model for early psychosocial support that may mitigate the risk of PICS-F. On a methodological level, this trial aims to generate high-quality evidence through a rigorous design. Regarding policy and practice, demonstrating the effectiveness of this low-cost, preventive intervention could inform clinical guidelines and support the implementation of family-centered care in critical care settings.

### Limitations

3.1

The potential limitations of this study encompass the risk of attrition during the 90-day follow-up period. Specifically, post-discharge from the hospital, the collection of data may become increasingly challenging. Furthermore, the single-center design of this study, constrained by limited financial and human resources, will restrict the generalizability of the findings.

## Conclusion

4

This protocol outlines the rationale and design for a RCT evaluating the efficacy of the SAF-T intervention—a brief, structured psychological program—in preventing PICS-F among family members of critically ill ICU patients. By employing a rigorous methodological framework that includes an active control group, longitudinal assessment, and comprehensive plans for fidelity monitoring and safety management, the study aims to generate high-quality evidence on the potential of early, scalable psychosocial support. If proven effective, the SAF-T intervention could provide a feasible model for integration into routine critical care practice, ultimately contributing to improved family well-being and the advancement of family-centered care.
